## Introduction

 Gastrointestinal (GI) cancers are a leading cause of global morbidity and mortality^1 2^ and induce significant costs to health services.^3^ Surgical intervention (eg, resection) is a primary treatment for GI cancers.^4^ However, surgery carries the risk of complications, risks which are increased for individuals with obesity.^5 6^ Consequently, patients with obesity are advised to lose weight prior to surgery.^7^ Previous research has shown that weight loss is feasible in a pre-surgery context for cancer patients^8^ and does not lead to increases in length of stay or postoperative complications.^9 10^ Indeed, a recent randomised controlled trial feasibility study investigating intentional pre-surgery weight loss in colorectal cancer patients reported no difference in complications between the weight loss and usual care group, and that those who lost more than 3.2% of their body weight had a 50% reduction in surgical complications.^11^

However, although weight loss may make the surgical procedure easier for surgeons to perform and/or reduce the risk of surgical complications, the effects of weight loss must be viewed within the context of the whole cancer patient journey. Indeed, greater preoperative weight loss is associated with worse long-term outcomes such as mortality and disease recurrence in upper GI and colorectal patients.^1012^,^14^ A possible explanation is that weight loss prior to surgery, particularly rapid weight loss, may result in the reduction of not only fat mass but also muscle mass, which is associated with increased mortality^15^ and is linked to metabolic disease.^16^ Additionally, low muscle mass has been associated with post-operative complications in cancer patients undergoing gastric surgery.^17^ Estimates suggest that one in two people with cancer will experience cachexia,^18 19^ which causes approximately 20–30% of all deaths in cancer patients.^20 21^ Consequently, interventions with the potential to exacerbate cachexia require thorough evaluation prior to adoption.

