Therefore, presurgery weight loss offers potential benefits and drawbacks that may be dependent on the actual body composition changes that occur; lower fat mass might be beneficial for reducing surgical complications, but reduced muscle mass is likely detrimental for overall morbidity and mortality. Until the effects of preoperative weight loss are better understood, it may not be appropriate to encourage patients to lose weight.^22^ A greater understanding of these factors would help to generate evidence-based recommendations for cancer patients providing much needed guidance for dietitians and specialist exercise professionals working with people affected by cancer.

Current recommendations advocate for prehabilitation programmes for cancer patients,^23^ which is the use of targeted interventions between the time of diagnosis and acute treatment to promote health and reduce the risk of future impairments.^24^ Prehabilitation interventions including exercise, nutrition and psychological support (either alone or in combination) have been shown to improve patient outcomes such as surgical complications, length of hospital stay and quality of life compared with usual care, and thus should be considered in standard care.^25^ Indeed, the National Cancer Plan for England acknowledges the importance of cancer prehabilitation and sets out the ambition to deliver a national ‘digital first’ prehabilitation offer by 2028.^26^ Therefore, investigating the effects of preoperative weight loss within a prehabilitation service will provide valuable information that could benefit individuals within this type of service.

Active Together is a multimodal prehabilitation and rehabilitation service in South Yorkshire, UK, which provides support to cancer patients to prepare for and recover from treatment.^27^ The service, which was co-designed by cancer patients, clinicians, professionals and academics, provides exercise, nutrition and psychological support to patients throughout the cancer care journey, spanning from prehabilitation before and during treatment to restorative and supportive rehabilitation after treatment.^28^ Patients are referred to the service after diagnosis where they undergo assessments to ascertain their physical, nutritional and psychological status, before receiving person-centred support underpinned by behaviour change techniques.^28^

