**Figure 2 F2:**
[figure not shown]
Directed acyclic graph for investigating the effect of body composition changes on surgical outcomes. Baseline and preoperative well-being include nutritional status, psychological well-being and physical fitness.

Pearson (or Spearman, depending on the distribution of the data) correlation coefficients will be calculated to explore associations between outcome measures (eg, body weight, size and shape, body composition, body mass change, PG-SGA-SF, EQ-5D-5L, etc) and clinical outcomes (eg, surgical complications, length of stay, number of emergency readmissions and length of operating time). P values <0.05 will be considered statistically significant. Linear and multivariate regression models will then be used to investigate the strength of associations between preoperative changes in patient body measures (eg, body weight and composition), self-reported outcomes (ie, questionnaire data) and clinical outcomes. Additionally, exploratory analyses comparing outcomes between groups of participants (eg, those that lose weight vs those that do not) will be completed, with groups created using thresholds used in the previous literature^10^ and/or data-driven approaches such as a median split^11^ or optimal cut-point determination^32^.

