Separate linear regression models will be created to investigate the amount of variation in self-reported and clinical outcomes which are explained by preoperative changes in patient body measures. Then, multivariate regression models will be created which combine patient outcome measures that contribute significantly to the estimation of clinical outcomes. Ordinal logistic regression models will also be used to explore the relationship between patient outcome measures and ordinal clinical outcome variables, such as surgical complications (Clavien-Dindo classification) and the surgical approach used. Where the distribution of data indicates it would be appropriate (ie, for non-linear relationships between predictor and outcome variables), other regression approaches such as restricted cubic splines or generalised additive models will be used. Regression analyses are appropriate as this is exploratory research, and this approach allows the observation of relationships between all variables. The regression models will all be adjusted for the variability in time between the assessment points, tumour group and pretreatment therapies where these are shown to reduce residual variance and not introduce collinearity to the model. Any outliers will be investigated to ensure that they are legitimate observations; only implausible data will be removed.

Multiple regression models will be assessed for multicollinearity between input variables using variance inflation factor and tolerance collinearity statistics and for independence of errors using the Durbin-Watson test statistic. If the largest variance inflation factor value is >10, or tolerance values are below 0.2 this could indicate potential issues in the model associated with multicollinearity. Also, if Durbin-Watson values differed significantly from two this would suggest dependence of errors between input variables in the model. Additionally, regression assumptions (eg, homoscedasticity, normally distributed errors) will be checked via diagnostic plots, and transformations of variables will be used if assumptions are not met.

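### Letting the data choose a linear or curved form, then admitting measures to the combined models by significance, inflates type I error and can drop a body-change exposure whose relation reverses mid-range

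*Protocol article*

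**What the plan says.** All of this stands in the protocol article, Statistics and analysis, in the text after Figure 2.

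- First step: "Pearson (or Spearman, depending on the distribution of the data) correlation coefficients will be calculated to explore associations between outcome measures" and clinical outcomes, with p below 0.05 counted as significant.
- Second step: "Separate linear regression models will be created to investigate the amount of variation in self-reported and clinical outcomes which are explained by preoperative changes" in body measures.
- Third step: "multivariate regression models will be created which combine patient outcome measures that contribute significantly to the estimation of clinical outcomes".
- Curved terms: "Where the distribution of data indicates it would be appropriate (ie, for non-linear relationships between predictor and outcome variables), other regression approaches" are to be used, with restricted cubic splines and generalised additive models as the examples.

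The section calls the work exploratory. It also plans group comparisons based on published thresholds, a median split or an optimal cut-point. Its sample-size paragraph rests on a linear regression with six predictors (f2=0.15, N=98) and a correlation of 0.3 (N=84), and plans 100 participants.

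The Introduction says that "presurgery weight loss offers potential benefits and drawbacks" and that these may depend on what tissue is lost. It reports fewer surgical complications in those who lost more than 3.2% of body weight, and for later outcomes that "greater preoperative weight loss is associated with worse long-term outcomes such as mortality and disease recurrence".

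**The concern.** Two stated rules act together.

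1. **Choice of form.** Whether an exposure enters as a straight line or a curve depends on how the data look. A p-value computed after that choice does not keep its nominal level, and the article states no correction. The stated trigger, the distribution of the data, is also loose: a variable's distribution does not show the shape of its relation to an outcome.
2. **Choice of measures.** The combined models take measures that earlier contributed significantly. Pearson, Spearman and a single linear term all respond to a one-directional trend. If the trend reverses near the middle of the observed changes, these tests have little power. Unless the trigger for curvature fires, the measure can then be left out of the combined model.

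Body mass and composition change are the exposures the study exists to examine. The risks are a null statement about one of them that reflects only the straight-line form, and curved findings presented at 5% that were not tested at 5%.

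**Working it through.** **Inputs from the article:** N=100, alpha 0.05, f2=0.15, six predictors, rho=0.3.

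**Assumptions (not in the documents):** a normally distributed exposure; a continuous outcome that is quadratic in the exposure; R2 = f2/(1+f2) = 0.15/1.15 = 0.13. The location of the turning point is varied. Where a percentage scale is used, weight change has mean -3% and SD 4%.

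**The plan's own figures.**
- Regression: non-central F with lambda = f2 x N = 0.15 x 98 = 14.7 on 6 and 98-7 = 91 df gives power 0.804, so N=98 is reproduced. At N=100 the power is 0.813.
- Correlation: ((1.960+0.842)/atanh 0.3)^2 + 3 = 84.9, so 85. A t-based version gives 82. The stated 84 lies between them.

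**Simulation.** N=100, 5,000 replicates per alternative and 20,000 under the null. The spline has 3 knots at the 10th, 50th and 90th percentiles and is tested jointly on 2 df. The pretest rule uses the spline test if the 1-df non-linearity test has p<0.05, and otherwise the linear test.

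| Truth | Pearson/linear | Spearman | Fixed spline | Non-linearity test | Pretest rule |
|---|---|---|---|---|---|
| No association | 0.051 | 0.050 | 0.051 | 0.051 | 0.074 |
| Straight line | 0.960 | 0.940 | 0.922 | 0.047 | 0.961 |
| Turn at the mean | 0.107 | 0.056 | 0.882 | 0.916 | 0.883 |
| Turn 0.5 SD off (31% beyond) | 0.541 | 0.471 | 0.882 | 0.813 | 0.884 |
| Turn 1 SD off (16% beyond) | 0.836 | 0.788 | 0.901 | 0.536 | 0.916 |
| Turn 1.5 SD off (7% beyond) | 0.905 | 0.877 | 0.908 | 0.329 | 0.935 |

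**On the percentage scale.** A turn at -3.2% lies (-3.2+3)/4 = -0.05 SD from the mean. Power there is 12% linear, 7% Spearman and 88% spline. A turn at -7% is (-7+3)/4 = -1 SD and one at -9% is -1.5 SD. Linear power there is about 84% and 91%.

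**Type I error.** The pretest rule gives 0.074 here, and 7-8% across the separate runs. If a finding is declared when either the linear or the non-linearity test is significant, it is 0.10.

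**Cost of extra spline terms on the article's omnibus calculation (f2 held at 0.15, N=100).** Six predictors: 0.813. Seven: 0.785 (80% power needs N=103). Eight: 0.758 (80% power needs N=109).

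**The case against.** **The plan already provides for curvature.** This stands. If the trigger is run as a non-linearity test, power is about 0.88 to 0.94 at every turning point, as good as the fixed spline. The gain from fixing the form in advance is therefore correct error rates and protection of key exposures from the screen, not a capability the plan lacks.

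**A reader might infer that the plan would mostly miss a pattern in which moderate loss helps and larger loss harms, and that the Introduction predicts it.** The documents do not support that. The Introduction places benefit on surgical complications and harm on mortality and recurrence, and attributes the difference to fat versus muscle. Opposite straight lines for different outcomes or tissues would fit that account. A U-shape on one outcome is an inference. The 3.2% figure is a level above which fewer complications were seen, not an optimum beyond which results worsen. Linear power is low only for a turn near the centre. At 1 SD or more the association is usually detected, although the non-linearity test then shows the reversal only 54% of the time or less.

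**The screen is narrower than it may seem.** This also stands. Correlation p-values do not decide which measures are regressed, the separate models are fitted regardless, and the significance condition is not confined to linear terms. It governs entry to the combined models only.

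**Exploratory work, with details left to an analysis plan.** Missing knots or degrees of freedom are no finding. The point concerns two rules the article does state. The exploratory label lowers the stakes, but the article still sets a 5% significance level and uses significance to select measures.

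**Group comparisons as a safeguard.** They help little here. With the turn at the mean, a median split has about 6% power, and an optimal cut-point search over the central 60% of values has a type I error of about 28%.

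**Conclusion.** The point holds in limited form. The stated data-driven choice of form raises the type I error of a nominal 5% test to about 7-8% if made by a non-linearity pretest, and to about 10% if either test may count. The significance screen can keep a body-change exposure out of the combined models when its relation reverses near the centre of the observed changes: linear power is about 12%, against 88% for a spline fixed in advance.

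The power figures rest on an assumed normal distribution of change, a quadratic relation, a continuous outcome and the plan's medium effect. They do not carry over directly to Clavien-Dindo grades. How likely such a reversal is cannot be judged from the documents. The change is worth making because it is cheap and concerns the study's main exposures.

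**What to change.** In the protocol article, Statistics and analysis:

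1. For continuous outcomes, pre-specify body mass change as a 3-knot restricted cubic spline with knots at fixed percentiles (for example the 10th, 50th and 90th). In a separate model, do the same for fat change plus fat-free change. Do not put all three together, because mass change is the sum of the other two.
2. Report the overall test, the non-linearity test and the fitted curve, with the linear estimate as secondary. For these exposures, remove the rule that lets the data choose the form.
3. Keep these exposures in the combined models whatever their univariable p-value.
4. For sparse ordinal outcomes such as Clavien-Dindo, a linear term may be kept if it is fixed in advance.
5. Restate the sample-size paragraph. On its omnibus calculation, power at N=100 falls from 0.81 (six predictors) to 0.785 with one spline (seven) or 0.758 with two (eight). State this rather than enrol more; the article describes 100 as what the service can be expected to supply in the time available.

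The cost is wording, one degree of freedom per splined exposure, and about 4 points of power for a single exposure if the relation is truly linear (96% to 92%). Composition models may run on fewer participants, since the article expects some visit 2 data to be missing, so their power would be lower still.

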**Ethics and dissemination:**

Ethical approval has been obtained from the Health Research Authority (Integrated Research Application System project ID 361634; Research Ethics Comittee reference 26/YH/0019). Written informed consent will be obtained from all participants. Data will be processed in accordance with General Data Protection Regulations and the Data Protection Act 2018. Findings will be disseminated via peer-reviewed publications, conference presentations and patient and public involvement activities.

STRENGTHS AND LIMITATIONS OF THIS STUDYThe observational nature of the study provides an ecologically valid insight into patient outcomes in an evidence-based cancer prehabilitation service.Longitudinal assessment of body mass and composition, surgical outcomes, physical fitness, nutritional status and quality of life allow investigation of the relationships between the changes in each metric across the perioperative period.The observational nature of the study precludes the ability to draw causal inferences.The potential heterogeneity of participant characteristics and treatment pathway may confound the associations reported; however, these will be accounted for statistically where possible.

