## Methods and analysis

### Study design

This is a prospective observational study to assess changes in patient body weight and composition during the preoperative phase of GI cancer treatment and the associations these have with surgical outcomes, physical fitness, nutritional status and quality of life. Recruitment and data collection for this study will take place between April 2026 and February 2027. Participants will complete two data collection sessions for this study: once as soon as possible after diagnosis and once within the 2 weeks prior to surgery. The time between the first and second visits will vary depending on tumour location, wait times for surgery and length of neo-adjuvant treatments (if applicable).

As well as these two data collection sessions, participants will continue to receive their usual care from the Active Together (p)rehabilitation service, which includes assessments at pre-defined time points throughout their cancer care journey. The data collected from these assessments will be used for this study, as well as surgical data that will be collected from the surgical team and hospital records. Figure 1 provides an overview of the timing and type of data collected from each source, and the Procedures section details the outcome measures collected from each source.

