### Statistics and analysis

Directed acyclic graphs have been created for the outcome measures in this study to identify confounding factors and determine which variables to adjust for during analysis. Figure 2 shows the causal pathway and potential confounders for investigating the effect of body composition changes on surgical outcomes. Online supplemental material 3 includes directed acyclic graphs for preoperative well-being, post-treatment well-being and 1-year survival. All quantitative data will be treated as continuous data, excluding Clavien-Dindo classification of postoperative surgical complications (ordinal) and the surgical approach, type of surgical complications and treatment pathway (nominal).

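### Adjustment for interval, tumour group and pretreatment therapies depends on model fit and collinearity, which can drop a confounder that the causal graphs were meant to fix

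*Protocol article*

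**What the plan says.** The Statistics and analysis section of the protocol article opens with directed acyclic graphs, built "to identify confounding factors and determine which variables to adjust for during analysis". One graph is Figure 2; the others are in a supplement. Neither is shown in the text at hand.

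Later in the same section, all regression models are to be "adjusted for the variability in time between the assessment points, tumour group and pretreatment therapies", but only "where these are shown to reduce residual variance and not introduce collinearity to the model". That sentence does not refer back to the graphs.

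The next paragraph sets the collinearity limits: "If the largest variance inflation factor value is >10, or tolerance values are below 0.2 this could indicate potential issues" in the model. The section also plans ordinal logistic regression for the Clavien-Dindo grade.

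Two other places bear on whether these covariates matter. Study design says the gap between visits depends on tumour site, surgical waiting time and the length of neo-adjuvant treatment. The strengths and limitations box says: "The potential heterogeneity of participant characteristics and treatment pathway may confound the associations reported". It promises to account for this statistically where possible.

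**The concern.** A confounder is related to both exposure and outcome. Whether to adjust for it is settled by its place in the causal structure, which is why the graphs were drawn. Whether it lowers residual variance in one sample of 100 is a different question. The more a confounder overlaps with weight change, the less residual variance it removes once weight change is in the model, and the more collinear it looks. Both conditions therefore weigh against covariates that are tightly linked to the exposure.

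The protocol gives grounds to expect such links. The interval between visits is the window in which weight changes, and it depends on tumour site and neo-adjuvant treatment. Collinearity among those covariates alone would not make the weight-change coefficient less precise, yet the rule as worded could still exclude one of them for it.

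At stake is the study's main question, the association between preoperative body changes and outcomes, which is to be judged at P<0.05. If treatment pathway drops out of a model, its effect is partly credited to weight change, and the reported P value takes no account of the selection step.

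**Working it through.** **The plan's own figure.** For the overall F test with f² = 0.15, 6 predictors and alpha 0.05, the noncentrality is 0.15 × N. Power first reaches 0.80 at N = 98 (0.8035) and is 0.813 at N = 100. The stated 98 is reproduced and not disputed.

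**What the residual-variance condition means.** The residual sum of squares never rises when a term is added, so the condition has content only for the residual mean square. That falls exactly when the added term has |t| > 1. A stricter reading keeps the covariate only if P<0.05.

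**Simulation.** N = 100 is the planned size; everything else is assumed. Exposure X (weight change) has a true effect of zero. One confounder C has correlation r with X and a standardised effect b on an outcome with variance 1. There are 40,000 replicates, and the table covers the residual-variance condition alone.

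| r | b | C dropped, mean-square rule | Type I error | C dropped, P<0.05 rule | Type I error |
|---|---|---|---|---|---|
| 0.3 | 0.2 | 17.5% | 5.5% | 52.0% | 7.4% |
| 0.3 | 0.3 | 2.8% | 5.3% | 17.2% | 6.8% |
| 0.5 | 0.2 | 22.6% | 7.4% | 59.0% | 12.5% |
| 0.5 | 0.3 | 4.8% | 6.0% | 24.2% | 11.2% |
| 0.7 | 0.2 | 33.0% | 12.6% | 70.3% | 22.4% |
| 0.7 | 0.3 | 11.6% | 10.1% | 41.0% | 25.9% |

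With C always kept, type I error is 4.9% to 5.1% throughout. At fixed b, the chance of dropping C rises with r. At fixed r, a stronger effect on outcome makes C more likely to be kept. Averaged over replicates, the bias under the mean-square rule is small (at most 0.014 SD). The damage is mainly to the validity of the test. In a dataset where C is dropped, the expected bias is of the order b × r, for example 0.2 × 0.7 = 0.14 SD.

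**Collinearity limits.** Tolerance = 1/VIF, so tolerance 0.2 is VIF 5, and VIF 10 is tolerance 0.1. Any VIF above 10 has already crossed the tolerance limit. With one confounder, VIF = 1/(1 − r²), so VIF 5 needs |r| = √0.8 = 0.894 and VIF 10 needs |r| = √0.9 = 0.949. Below about 0.89, only the residual-variance condition can drop C.

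**Ordinal models.** The residual scale of a logistic model is fixed by the link and not estimated. The condition therefore cannot be applied to Clavien-Dindo grade as written.

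**Price of always adjusting.** The standard error of the exposure coefficient is multiplied by √VIF, before any gain from lower residual variance. At r = 0.7, VIF = 1/(1 − 0.49) = 1.96 and √1.96 = 1.40. At r = 0.92, VIF = 1/(1 − 0.8464) = 6.51 and √6.51 = 2.55.

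**The case against.** The strongest reply is that the two statements can coexist. The article never says that the three named covariates are the whole adjustment set or that the graphs are set aside. The conditional sentence may only govern extra precision covariates. The graphs are not visible, so nobody can confirm from this text that the three are confounders in them. This stands against the stronger reading that the rule replaces the graphs. It does not remove the problem: the rule covers all regression models, gives the graphs no priority, and names covariates that the article elsewhere treats as sources of confounding.

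Other inferences a reader might draw also fail:

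- That baseline values are left out of the adjustment. The Figure 2 caption places baseline well-being (nutritional, psychological and physical) in the graph, so an omission cannot be established.
- That the VIF and tolerance limits contradict each other. They are joined by an or and are said only to point to possible problems. The VIF limit is redundant, and neither number by itself orders a variable to be removed.
- That very high false-positive rates follow. Those need a correlation near 0.92, where one covariate explains about 85% of the variance in weight change, together with the covariate being dropped. The article supports neither assumption. Retention by significance test is likewise not stated for these covariates.

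The study is also exploratory and disclaims causal inference. That lowers the severity. It does not justify a rule that can discard a confounder already identified, when P<0.05 is the declared threshold and the stated motive is to inform advice on preoperative weight loss.

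**Conclusion.** The point holds in a limited form. The plan assigns adjustment to causal graphs and then makes it conditional, for three likely confounders, on criteria that do not measure confounding and are undefined in the ordinal models. Followed as written, the rule can drop a true confounder; it need not do so.

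The effect is negligible if the covariates are weakly related to weight change, and roughly a doubling of the nominal 5% error rate or a little more at a correlation of 0.7. If retention were by significance, it would be about 22–26% at that correlation. These figures rest on one confounder, a linear model and assumed correlations and effects, none of which the article gives. This should be fixed, but it is not a critical fault.

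**What to change.** In Statistics and analysis, replace the conditional clause with a statement that every model keeps the confounders identified by its own graph, whatever their effect on residual variance or collinearity. This includes interval, tumour group and pretreatment therapies wherever the graph marks them as confounders. State that collinearity is a reported diagnostic with one limit (tolerance below 0.2, which is VIF above 5) and never a reason to drop a confounder.

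The edit is to wording, but it has a statistical price. Intervals widen when a confounder is closely tied to the exposure: the standard error is about 1.4 times larger at a correlation of 0.7 and about 2.5 times at 0.92. Tumour group and therapy may each need several category terms, which could exceed the 6 predictors in the sample-size calculation. On the same overall F test, 7 predictors need N = 103 and 8 need N = 109. At N = 100, power would be 0.785 and 0.758. Coding these covariates economically, or acknowledging the small loss, would deal with this.
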